#### PHC professional’s characteristics

2.5.2

We will collect the following characteristics from the healthcare professionals: age, gender, time worked in PHC, time worked at the center, number of work hours per week, professional category, number of assigned patients to their list, employment status (permanent, temporary), work shift (morning, afternoon, both), participation in on-call duties, perceived health status, job satisfaction on a scale from 0 to 10.

#### Patient characteristics

2.5.3

Age, gender, educational level, nationality, employment status, number of visits to the PHC center in the last 12 months, duration of registration at the center, self-perceived health status, number of medications, and presence of chronic diseases.

### Sample size

2.6

The sample size calculation is based on the primary outcome variable of this trial, the rate of avoidable hospitalizations. To achieve a statistical power of 80% with an alpha risk of 0.05 in a one-sided test, a total of 118 healthcare centers (59 in the intervention group and 59 in the control group) are required to detect a difference equal to or greater than 1.5 units in the rate of avoidable hospitalizations per 1,000 patients, corresponding to a 15% reduction in the rate of avoidable hospitalizations (Cohen’s d = 0.49). Based on the results of our previous study (31), we assume a mean rate of 11.2 and a standard deviation of 3.3. A follow-up loss rate of 0.5% has been estimated.

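### The sample-size target of 1.5 per 1,000 is labelled a 15% reduction and d = 0.49, but the stated mean and SD make it 13.4% and d = 0.455

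*Protocol article*

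**What the plan says.** All the figures are in section 2.6 (Sample size) of the protocol article, which is the document's only statement of target effect and power.

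- Test and power: "To achieve a statistical power of 80"%, with "an alpha risk of 0.05 in a one-sided test".
- Size: "a total of 118 healthcare centers (59 in the intervention group and 59 in the control group) are required".
- Target, absolute and relative: a "difference equal to or greater than 1.5 units in the rate of avoidable hospitalizations per 1,000 patients, corresponding to a 15% reduction".
- Target, standardised: Cohen's d = 0.49, in brackets after the percentage.
- Inputs, taken from the team's previous study: "we assume a mean rate of 11.2 and a standard deviation of 3.3".
- Loss: "A follow-up loss rate of 0.5% has been estimated".

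The planned primary analysis (section 2.8.3, Statistical analysis) is a linear regression of the centre-level rate at 24 months, adjusted for the baseline rate. Section 2.6 gives no baseline-to-follow-up correlation.

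**The concern.** One effect is described in three ways, and the text presents the three as equivalent. With a mean and an SD also stated, the equivalence can be checked, and it fails. This is a misstatement of figures that are given, not a detail that an article leaves to a fuller document.

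At stake is the benchmark for the primary outcome. The percentage is the figure readers will carry forward. If the final report compares its estimate or confidence interval with a 15% reduction, it will be using a larger effect than the one behind the 118 centres. A reader who wants the true design target has to redo the calculation, and even then cannot rule out that the mean or SD is the wrong entry.

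**Working it through.** **Inputs** (all from section 2.6): difference 1.5 per 1,000; relative reduction 15%; d = 0.49; mean 11.2; SD 3.3; one-sided alpha 0.05; power 80%; 59 centres per arm; loss 0.5%.

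**Step 1. Reproduce the stated size.** For two means under the normal approximation, n per arm = 2(z₀.₉₅ + z₀.₈₀)² / d².

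With d = 1.5/3.3 = 0.4545: n = 2 × (1.645 + 0.842)² / 0.4545² = 59.85, so 60 per arm and 120 in total, or 121 after 0.5% loss (120/0.995 = 120.6). The plan says 118, which is within 3%. The smallest difference detectable with 80% power at 59 per arm is 2.486 × √(2/59) × 3.3 = 1.51 units. So 1.5 units with SD 3.3, one-sided, is very close to what 118 centres deliver.

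**Step 2. Convert each description with the stated mean and SD.**

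| Starting point | Units per 1,000 | % of 11.2 | d (units/3.3) |
|---|---|---|---|
| 1.5 units | 1.50 | 1.5/11.2 = 13.4% | 1.5/3.3 = 0.455 |
| d = 0.49 | 0.49 × 3.3 = 1.62 | 1.617/11.2 = 14.4% | 0.49 |
| 15% | 0.15 × 11.2 = 1.68 | 15% | 1.68/3.3 = 0.509 |

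The rows describe three different effects. The 15% and d = 0.49 labels do not agree with each other either.

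**Step 3. Could rounding explain it?** Let each input range over its rounding interval: difference 1.45 to 1.55, mean 11.15 to 11.25, SD 3.25 to 3.35.

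- Relative reduction: 1.45/11.25 = 12.9% to 1.55/11.15 = 13.9%.
- d: 1.45/3.35 = 0.43 to 1.55/3.25 = 0.48.

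Neither 15% nor 0.49 is reached. For 1.5 units to match both labels, the mean would have to be 1.5/0.15 = 10.0 and the SD 1.5/0.49 = 3.06.

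**Step 4. Which version gives 118?** SD 3.3, 80% power, normal approximation; totals are before and after 0.5% loss.

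| Version | Total, one-sided | Total, two-sided | One-sided power at 59 per arm (normal / noncentral t) |
|---|---|---|---|
| 1.5 units | 120 / 121 | 152 / 153 | 79.5% / 79.1% |
| d = 0.49 | 104 / 105 | 132 / 133 | 84.5% / 84.2% |
| 15% | 96 / 97 | 122 / 123 | 86.9% / 86.5% |

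Under the one-sided test that the section states, only the 1.5-unit version comes near 118. The nearest rival is 15% tested two-sided (122 to 123), which is further from 118 and contradicts the stated sidedness.

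**Step 5. Effect of the planned baseline adjustment.** Adjustment scales the residual SD by √(1 − r²), where r is the correlation between baseline and 24-month rates. The document gives no r, so this range is an assumption. Noncentral-t power at 1.5 units with 59 per arm is 79.4% at r = 0.1, 80.5% at r = 0.2, 82.3% at r = 0.3 and 88.3% at r = 0.5.

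**The case against.** The strongest reply is that the design is unharmed. Section 2.6 makes 1.5 units the difference to be detected; the percentage and d are attached as restatements, and the 118 centres do not rest on them. Both labels err upwards, so if the true effect were 15% or d = 0.49, the trial would have more than 80% power. Nothing in the randomisation, outcome or analysis sections uses either label. All of this stands, and it limits the consequence to wrong figures in the text.

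A reader might infer more, in three ways that the document does not support:

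- **That the powered effect is undefined.** It is not. The wording and the arithmetic both point to 1.5 per 1,000.
- **That 118 is too few.** The formulas give 60 per arm (normal approximation) or 61 (t-test) against 59, which is about 79% power instead of 80%. That is for an unadjusted comparison. The planned adjustment removes the gap at an assumed correlation of about 0.2.
- **That the loss allowance was left out.** At 0.5%, the allowance is 0.6 of a centre in 118, too small to show in a rounded total.

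What the reply does not answer is that two of the three published descriptions of the primary target are wrong on the section's own inputs, and both make the target look larger than it is.

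**Conclusion.** The inconsistency is real and rounding does not explain it. On the stated mean and SD, the target of 1.5 per 1,000 is a 13.4% reduction and d = 0.455. The 15% label overstates it by 1.6 percentage points (0.18 units) and the d label by about 0.035 (0.12 units). The target is recoverable as 1.5 per 1,000, with about 79% one-sided power at 59 per arm before baseline adjustment.

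This takes 11.2 and 3.3 as the values actually used. They come from a previous study that is not shown here, so a transcription error in the mean or SD cannot be excluded. In that case the labels might be right and the inputs wrong. Either way the paragraph needs correcting, because it is the only statement of what the primary comparison was designed to detect. The number of centres is not in question.

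**What to change.** Check the figures in section 2.6 against the calculation that was actually run, then let every figure follow from one target.

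- If 1.5, 11.2 and 3.3 are right: state the target as 1.5 per 1,000, a reduction of about 13.4%, d about 0.45, with about 79% one-sided power for 118 centres before baseline adjustment. Remove 15% and d = 0.49.
- If the mean or SD was mis-entered: correct it, and re-derive the percentage, d and power from the corrected value.

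Replacing 1.5 with 1.68 just to keep the 15% label would not be an equivalent repair. It would change the target, and 118 would no longer be the number required for 80% power.

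The cost is one reworded paragraph. If the inputs stand, the stated effect size becomes slightly less favourable. No extra centres and no change to the design or analysis are needed.

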### Randomization of PHC centers

2.7

After recruiting the centers and collecting baseline data, they will be randomly assigned to either the control group or the intervention group in a 1:1 ratio. This randomization process will be performed using specialized software that generates a list of random numbers by a statistician not otherwise involved in the study data collection. Blinding of center allocation to the PHC professionals will not be possible due to the characteristics of the intervention. To ensure balance and representation, we will apply stratified randomization, a well-established approach to balance one or a few prespecified prognostic characteristics between treatment groups (40, 41). We identified two prognostic characteristics that could be strongly associated with the primary outcome of the trial: the healthcare region the PHC belonged to (which determines the intensity and types of safety improvement initiatives routinely conducted by regional healthcare managers), and being or not an accredited PHC teaching center (as teaching centers are frequently more easily engaged in improvement activities). To help ensure the balance of treatments within strata and the balance of strata within treatment groups, the assignment procedure within each stratum will be restricted using permuted blocks (41).

### Evaluation of the effectiveness of the SinergiAPS intervention

2.8

Our first objective is to evaluate the effectiveness of the intervention at 24 months in improving the safety of the healthcare provided in the PHC centers. We will examine the impact of the intervention on the following outcome measures:

#### Primary outcome measure

2.8.1

The rate of avoidable hospitalizations will be assessed based on the definition provided by the Agency for Health Research and Quality, based on data extracted from the Minimum Basic Data Set using predefined ICD-9 codes (42). The rate of avoidable hospitalizations will be calculated specifically for conditions such as asthma, chronic obstructive pulmonary disease, congestive heart failure, angina, diabetes, and chronic kidney disease. For each participating center, we will obtain the total number of registered patients and the total number of avoidable hospitalizations recorded during the previous 12 months.

#### Secondary outcome measures

2.8.2

Perceptions and experiences of patients (scores from the scales of the PREOS-PC Compact questionnaire): This questionnaire will be administered to a selected sample of 100 patients from each healthcare center. This sample size is estimated to achieve a reliability of at least 0.7 in the mean scores of the healthcare centers for the questionnaire’s scales. The questionnaire incorporates the following scales:
“Practice activation”: 4 items (Cronbach’s α = 0.71) that measure the proactivity of healthcare centers towards patient safety.“Experience of harm (severity)”: 3 items (Cronbach’s α = 0.81) that assess the level of harm suffered by patients because of the healthcare they received.“Burden of harm”: 3 items (Cronbach’s α = 0.80) that evaluate the impact and consequences of the harm experienced by patients.“Overall assessment of the center’s safety level” (1 item). Visual analogue scale.
Patient safety culture of healthcare professionals: We will calculate the average center-level score of the Patient Safety Culture Composite Score (ranging from 1–5 points), based on the responses of professionals to the Spanish version of the Medical Office Survey on Patient Safety Culture (MOSPSC) questionnaire (39).Adverse events experienced by healthcare professionals in the last 12 months: An ad hoc questionnaire will be adapted from a previous study (43) to assess the adverse events experienced by professionals (frequency and impact on healthcare professionals’ well-being).Number of actions aimed at improving patient safety in the center in the last 12 months: An ad hoc questionnaire will be administered to the quality and patient safety referent of each center, including both intervention and control centers, to determine the number of actions taken to enhance patient safety.

#### Statistical analysis

2.8.3

Initially, we will conduct descriptive statistical analysis to characterize the participating healthcare centers. For each of the two groups (control and intervention), we will calculate frequencies (percentages) for binary or categorical variables, and medians (along with interquartile range) for continuous variables. The effectiveness of the intervention will be analyzed by comparing the mean score of the primary outcome variable (rate of avoidable hospitalizations) between the control and intervention groups after 24 months of follow-up. A linear regression model will be used, including the baseline rate as an adjusting variable. Moreover, stratified effectiveness analyses will be performed based on baseline audit scores. This approach will enable us to measure the independent effect of the intervention in centers with different levels of potential improvement according to the audit results. All analyses will be conducted on an intention-to-treat basis by a statistician blinded to group allocation, ensuring that participants are analyzed according to their assigned group irrespective of any deviations from the intervention. If necessary, we will handle missing data with multiple imputation. An equivalent methodology will be applied for the secondary outcome variables. All outcome variables (including scores from patient and healthcare professional questionnaires) will be analyzed at the level of healthcare centers (mean score per center). Regarding PREOS-PC scores, we will explore the extent to which the different methods of administration of the questionnaire (face-to-face, telephone, or by email) could yield systematic differences in the scores obtained. In case they do, to minimize a potential confounding bias, we will include the method of administration as an adjustment variable in our regression model. All analyses will be carried out in Stata 14.1 (Stata Corp), using an α of 5% throughout.

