### Participating healthcare centers and sampling

2.3

The study units in this trial are public PHC centers from any autonomous community in Spain that agree to participate through informed consent (Supplementary file 2). Centers that exclusively provide specific services (such as pediatrics or women’s health centers), and centers that have been established for less than 12 months at the time of recruitment will be excluded.

Recruiting PHC centers: We will recruit PHC centers from various regions in Spain. Each participating node will recruit centers from their own community and, whenever possible, from neighboring regions. To ensure a broad geographic representation, researchers from seven regions (Balearic Islands, Catalonia, Andalusia, Madrid, Castilla y León, Aragon, and Galicia) are involved in this multicenter study. In regions where we do not have a specific node or researcher, we will leverage our extensive network of key informants, including researchers from the Patient Safety Group of SEMFYC, the research boards of SEMFYC, and the national network of the European General Practice Research Network. This established network will significantly aid in identifying and engaging suitable healthcare centers for participation in this study. The study proposal will be presented to the relevant territorial management authorities and healthcare centers to garner support and participation. A healthcare center will be considered recruited once informed consent is obtained from the center coordinator.

Sampling of PHC centers: For each region, an intentional sample of centers will be selected, aiming for heterogeneity in terms of size, rurality, and inclusion of both teaching and non-teaching centers.

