#### PHC center characteristics

2.5.1

We will collect the following information for each center (Table 1): total number of visits in the last 12 months, total count of registered patients at the center, the patient-to-physician ratio, the percentage of patients aged over 65 years, the percentage of female patients, the academic affiliation (whether the center is a teaching center or not), the rurality index (37), deprivation index (38), and the distribution of patients according to adjusted morbidity group (39). This data will be sourced from healthcare information systems of the health services from the participating regions.

**Table 1 tab1:** Data collection schedule for the SinergiAPS 2 trial.

	Source	Aggregation level	Data collection timing
1. Characteristics of the primary healthcare centers (all recruited centers)			
Number of visits to the center in the last 12 months	Administrative data	Practice level	Baseline
List size (total number of registered patients at the center)	Administrative data	Practice level	Baseline
Average number of patients per physician in the center	Administrative data	Practice level	Baseline
Percentage of patients over 65 years old in the center	Administrative data	Practice level	Baseline
Percentage of female patients	Administrative data	Practice level	Baseline
Teaching center (yes/no)	Administrative data	Practice level	Baseline
Rurality index	Administrative data	Practice level	Baseline
Adjusted morbidity group (GMAs—percentage of patients in each of the five complexity groups)	Administrative data	Practice level	Baseline
2. Effectiveness evaluation (all recruited centers)			
Rate of avoidable hospitalizations during the previous 12 months (primary outcome measure)	Administrative data	Practice level (number hospitalizations/10000 registered patients)	Baseline and 24 months follow-up
Activation of healthcare centers: 4 items (Cronbach’s α = 0.70) that measure the proactivity of healthcare centers towards patient safety.	Patient-reported (PREOS-PC Compact)	Practice level (mean score—theoretical range: 0 to 100)	Baseline and 24 months follow-up
Experience of harm (severity): 3 items (Cronbach’s α = 0.85) that assess the level of harm suffered by patients as a result of the healthcare they received.	Patient-reported (PREOS-PC Compact)	Practice level (mean score—theoretical range: 0 to 100)	Baseline and 24 months follow-up

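### The primary outcome is a count over a known list size in centers chosen to differ in size, and the equal-weight linear model without the stratification factors is valid but gives up some precision

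*Protocol article*

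**What the plan says.** Section 2.8.1 collects numerator and denominator for every center: "we will obtain the total number of registered patients and the total number of avoidable hospitalizations recorded during the previous 12 months". Section 2.3 selects centers on purpose "aiming for heterogeneity in terms of size, rurality, and inclusion of both teaching and non-teaching centers". Section 2.8.3 then works with one rate per center: "The effectiveness of the intervention will be analyzed by comparing the mean score of the primary outcome variable", and "A linear regression model will be used, including the baseline rate as an adjusting variable". No weight, offset or count model is named.

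Section 2.7 stratifies the randomization by healthcare region and by teaching accreditation, because both are thought to be strongly related to the primary outcome. Neither is in the model of section 2.8.3.

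Section 2.6 sizes the trial on the center-level comparison: "To achieve a statistical power of 80% with an alpha risk of 0.05 in a one-sided test", 59 centers per arm, a difference of 1.5 per 1,000, mean 11.2 and SD 3.3.

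**The concern.** A rate based on a small list varies more by chance than one based on a large list. Equal-weight linear regression treats both as equally informative. Adjusting for the baseline rate removes stable differences between centers but not the chance variation of the follow-up count, so chance becomes a larger share of what remains. A model that uses count and list size could extract more from data already in hand. Leaving out the stratification factors also forgoes whatever outcome variation they explain, and they were chosen because they should explain some. What is at stake is precision, not validity.

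**Working it through.** **The plan's own figure.** Per arm, n = 2 × (3.3/1.5)² × (1.645 + 0.842)² = 59.85. The stated 59 gives 79.5% power, so the plan's figure is essentially reproduced. The SD of 3.3 is that of observed center rates from the previous study, so it already contains count noise.

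**Chance variation of one center's rate.** Poisson SD per 1,000 = √(11.2 / list size in thousands).
- List 2,000: √(11.2/2) = 2.37
- List 25,000: √(11.2/25) = 0.67
- Variance ratio: 25/2 = 12.5
- Share of the planning variance 3.3² = 10.89: 21% at 5,000, 10% at 10,000, 5% at 20,000

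**What equal weights cost in a linear model.** Let v be a center's Poisson variance, τ² = 10.89 − mean(v) the between-center variance, and ρ the correlation of true baseline and follow-up rates. After baseline adjustment the between-center part is about τ²(1 − ρ²). The efficiency of equal weights relative to weights 1/(between-center + Poisson variance) is [1 / mean(1/(τ²(1−ρ²)+v))] / [τ²(1−ρ²) + mean(v)].

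Example (assumed log-normal lists, median 10,000, CV 1.0): mean(v) = 1.58 and τ² = 9.31. At ρ = 0.9 the between-center part is 9.31 × 0.19 = 1.77. The average variance is 1.77 + 1.58 = 3.35, against 2.96 with optimal weights, so efficiency is 0.88.

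| Median list, CV | ρ = 0.5 | ρ = 0.8 | ρ = 0.9 |
|---|---|---|---|
| 20,000, 0.4 | 1.00 | 1.00 | 0.99 |
| 10,000, 1.0 | 0.98 | 0.94 | 0.88 |
| 5,000, 1.0 | 0.93 | 0.86 | 0.78 |

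Weighting by list size alone is not the answer. At median 10,000, CV 1.0 and ρ = 0.5 it keeps only 0.57.

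**Simulation of the models** (118 centers, mean 11.2, observed SD near 3.3, log-normal lists, 300 to 1,500 replicates per scenario). The squared ratio of mean z, negative binomial with offset over linear model, reads as a gain in effective sample size.

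| Median list, CV | ρ = 0.50 | ρ = 0.68 | ρ ≈ 0.91 |
|---|---|---|---|
| 12,000, 0.6 | 1.04 | 1.05 | 1.08 |
| 8,000, 1.0 | 1.05 | 1.07 | 1.20 |
| 5,000, 1.2 | 1.09 | 1.15 | 1.30 |

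The last column uses a between-center log SD of 0.25 and a period log SD of 0.08, hence ρ = 0.25²/(0.25² + 0.08²) = 0.91. Its mean z values are 4.60 to 4.77, 3.90 to 4.28 and 3.31 to 3.77.

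Poisson with offset and robust standard errors behaved differently. At median 10,000, CV 1.0 and ρ = 0.5 the ratio was 0.77, against 1.05 for the negative binomial. Poisson weights grow with list size without limit, whereas negative binomial weights level off as between-center variation takes over.

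Under the null, the linear and negative binomial models both rejected close to the nominal 5%.

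**The case against.** The strongest defense is that nothing here is an error. Centers are the randomized units, the trial is sized on the same center-level comparison, and type I error is sound. Equal weighting targets the average effect across centers, a legitimate question for a center-level intervention. Weights or extra covariates could be set in an analysis plan that is not shown. Simulated one-sided power of the linear model was 86% or more in all nine scenarios of the second table, above the 80% target. All of this stands, and it limits the point to efficiency.

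Four stronger readings are tempting, and the documents do not support them.
- That the linear model cannot address the target because section 2.6 mentions a 15% reduction. That section states the target first as an absolute difference of 1.5 per 1,000, which the linear model estimates directly.
- That a few small centers drive the result. With equal weights each center contributes roughly 1/59, about 1.7%, of its arm's mean.
- That a 20-30% loss is to be expected. This needs small, very unequal lists and a correlation near 0.9 between periods two years apart; the article gives neither.
- That any count model would do better. Poisson with robust errors can lose precision, and quasi-Poisson with scaled errors rejected up to 11% under the null in simulation.

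**Conclusion.** The point holds as a modest efficiency improvement. The planned analysis is valid and its stated power is not inflated by count noise. It gives up about 3-10% of effective sample size with medium or large lists and moderate baseline correlation, and up to about 20-30% only with small, very unequal lists and highly stable baseline rates. The negative binomial model was ahead of the linear model in every scenario run, often by only a few percent. The gain from adding region and teaching status is not quantified, because the article gives no figure for how much variation they explain.

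These sizes assume log-normal list sizes and the rate per 1,000 used in section 2.6. Table 1 gives the rate per 10,000. If 11.2 were per 10,000, equal weights would keep only about 51% to 97% of optimal efficiency at median lists of 15,000 to 25,000. A reader might infer the larger loss from this. However, at a list of 10,000 the Poisson variance alone would then be 11.2, above the planning variance of 10.89, so that reading does not fit the stated SD unless lists are large. The unit should be reconciled.

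**What to change.** Prespecify as primary a negative binomial regression of the 24-month count with log(registered patients) as offset, adjusted for baseline rate, region and teaching status. A linear model weighted by 1/(between-center variance + Poisson variance), with the same covariates, is an acceptable alternative. Report both the rate ratio and the implied absolute difference per 1,000, so that the result can be set against the 1.5 of section 2.6. State that the estimate leans toward larger centers. Keep the equal-weight linear model, also adjusted for region and teaching status, as the center-average sensitivity analysis. Do not substitute quasi-Poisson or list-size weighting.

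The cost is wording, since counts, list sizes, region and teaching status are already collected. The price is a shift of weight toward larger centers, a ratio as the main scale, and a few degrees of freedom: with the seven regions named in section 2.3, 6 + 1 = 7 further parameters for 118 centers.

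### Randomization is stratified by region and teaching status, but the stated model adjusts only for the baseline rate, so precision is lost to the extent that the strata predict the outcome beyond baseline

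*Protocol article*

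**What the plan says.** Protocol article, section 2.7 (Randomization of PHC centers), describes a stratified allocation: "we will apply stratified randomization, a well-established approach to balance one or a few prespecified prognostic characteristics between treatment groups". On the choice of factors it says: "We identified two prognostic characteristics that could be strongly associated with the primary outcome of the trial". The first is the health region, on the ground that regional managers differ in the safety initiatives they run. The second is "being or not an accredited PHC teaching center", on the ground that teaching centres are easier to involve in improvement work. Allocation is also blocked: "the assignment procedure within each stratum will be restricted using permuted blocks".

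Section 2.8.3 (Statistical analysis) specifies the primary comparison at 24 months: "A linear regression model will be used, including the baseline rate as an adjusting variable". It applies the same kind of analysis to the secondary outcomes. The only other covariate it names is conditional and applies to PREOS-PC scores alone: "we will include the method of administration as an adjustment variable in our regression model". The stratified effectiveness analyses in that section are by baseline audit score, not by the randomization strata. No other section brings region or teaching status into an outcome model.

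Table 1 lists the primary rate at baseline and at 24 months. It lists the number of safety improvement actions at 24 months only.

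**The concern.** Stratified, blocked allocation makes the arms nearly equal in their mix of regions and teaching centres. Differences between strata then contribute little to the error of the treatment contrast. A model without the strata still counts those differences as residual variation. Its standard error therefore describes a less precise experiment than the one that was run: intervals are too wide, and the test rejects less often than its nominal level under the null hypothesis.

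What is at stake is efficiency, in a trial whose unit of analysis is the centre and which has 118 of them. Validity is not at stake. The mismatch is between two explicit statements, since section 2.7 gives a prognostic reason for the strata and section 2.8.3 states an adjustment set that leaves them out.

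**Working it through.** **Inputs from the protocol article.** Section 2.6: difference 1.5 per 1,000, SD 3.3, 59 centres per arm, one-sided alpha 0.05, target power 80%. Section 2.3: "researchers from seven regions (Balearic Islands, Catalonia, Andalusia, Madrid, Castilla y León, Aragon, and Galicia) are involved in this multicenter study".

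**Assumptions, because the documents give no figure.** ρ is the correlation between the baseline and 24-month rates. R² is the share of the variance left after baseline adjustment that the strata explain. Seven regions crossed with teaching status are taken as 14 strata. The simulation uses blocks of 4.

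**1. The plan's own figure.** SE = 3.3 × √(2/59) = 0.608, and 1.5/0.608 = 2.469. One-sided power = Φ(2.469 − 1.645) = 79.5%. Solving for 80% gives 60 per arm, 120 in total, against the stated 118. So the sample size reproduces as an unadjusted comparison of two means, which uses neither baseline nor strata.

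**2. Excess in the standard error.** The ratio of the SE without strata to the SE with strata is 1/√(1 − R²):

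| R² | Ratio |
|---|---|
| 0.05 | 1.026 |
| 0.10 | 1.054 |
| 0.20 | 1.118 |

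**3. One-sided power for the baseline-adjusted model.** The residual SD is 3.3 × √(1 − ρ²) without strata, and that times √(1 − R²) with them. For ρ = 0.5 without strata, SE = 0.608 × √0.75 = 0.526, 1.5/0.526 = 2.851 and power = Φ(1.206) = 88.6%. With R² = 0.20, 2.851/√0.80 = 3.187 and power = Φ(1.542) = 93.9%.

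| ρ | Without strata | R² 0.05 | R² 0.10 | R² 0.20 |
|---|---|---|---|---|
| 0 | 79.5% | 81.3% | 83.1% | 86.8% |
| 0.5 | 88.6% | 90.0% | 91.3% | 93.9% |
| 0.7 | 96.5% | 97.1% | 97.7% | 98.7% |

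The column without strata slightly understates that model's power. If the strata are perfectly balanced, the estimate is itself less variable, and power without strata is Φ((2.851 − 1.645)/√(1 − R²)) at ρ = 0.5: 89.2%, 89.8% and 91.1% for R² of 0.05, 0.10 and 0.20. The gain from adding strata is then about 1 to 3 points, so the table's differences of about 1 to 5 points are upper figures. The true one-sided size of the nominal 5% test, 1 − Φ(1.645/√(1 − R²)), is 4.6%, 4.2% and 3.3%.

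**4. Simulation** (118 centres, 14 strata, blocks of 4, 4,000 runs per setting, baseline rate always in the model):

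| Setting | Model SE, without / with strata | One-sided size, without / with | One-sided power, without / with |
|---|---|---|---|
| Stable strata (20% of variance), within-stratum ρ 0.5 | 0.485 / 0.473 | 4.4% / 5.0% | 92.5% / 92.6% |
| Stable strata (20%), ρ 0.7 | 0.395 / 0.391 | 4.6% / 4.6% | 98.4% / 98.4% |
| As above, plus stratum-specific change worth 10% of variance | 0.415 / 0.366 | 3.3% / 5.2% | 98.4% / 99.1% |
| As above, plus change worth 20% | 0.436 / 0.339 | 2.4% / 5.0% | 98.1% / 99.6% |
| Strata 30%, no within-stratum ρ | 0.576 / 0.513 | 3.7% / 5.2% | 84.0% / 89.5% |
| Strata explain nothing, ρ 0.7 | 0.435 / 0.438 | 4.7% / 4.7% | 96.4% / 96.0% |

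In the two settings with stratum-specific change, the true sampling SD of the estimate without strata was about 0.375 and 0.356, against reported values of 0.415 and 0.436. In no setting did leaving the strata out raise the type I error above its nominal level.

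**5. The outcome without a baseline.** For the number of safety improvement actions, no baseline value can absorb stratum differences. The ratios in step 2 apply to whatever share of that outcome's variance the strata explain. The documents give no effect size or SD for it, so no power figure is possible.

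**The case against.** The strongest reply is that the baseline covariate is the same 12-month rate in the same centre, so stable regional differences are already in it. That stands as far as it goes: with stable strata, the simulated SE excess is 1–3% and the power loss about 0–1 point. It fails where strata change differently over 24 months, which the article's reasoning about regional safety initiatives makes plausible. It also fails for the outcome measured only at 24 months.

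Second, section 2.7 says that the factors could be strongly associated with the outcome, not that they are, and the reason given for teaching status concerns engagement as much as prognosis. This is fair, and it is why R² is shown as a range that includes negligible effects.

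Third, with about 8 centres per stratum (118/14), incomplete blocks leave some imbalance, so the formulas in step 3 are limiting values. This is correct, and the simulation allows for it.

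Fourth, an article need not list every covariate, and a separate analysis plan might add the strata. But the article does state an adjustment set, including a conditional term for one questionnaire. The point is about the model as stated.

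A reader might also infer that the trial has no power to spare and that this omission leaves it underpowered. The documents do not support that. The 118 centres come from a calculation without covariates, so any baseline correlation raises power above the planned figure. A two-sided calculation without baseline gives about 70% (69.5%), but the shortfall comes from changing the sidedness and ignoring the planned covariate, not from leaving out the strata.

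**Conclusion.** The point holds as a recommendation on efficiency. The design stratifies on two factors and the stated models ignore them. The consequence can only be conservative: standard errors too large, intervals too wide, some power lost. A reader who suspects bias or a raised false-positive rate will find neither.

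The size rests on two quantities that the documents do not give. Under R² of 5–20% the SE excess is about 3–12%. At ρ = 0.5 the one-sided power comparison is 88.6% against 90.0–93.9%, and the gain is smaller once the balance achieved by the design is credited to the model without strata. If baseline carries the strata, almost nothing is lost. In none of these cases does the omission itself push power below the planned 80%. The mismatch in the text is certain. The harm to the primary analysis is modest and conditional. The argument is strongest for the number of safety improvement actions, because both stated reasons for stratifying bear on it directly and it has no baseline adjustment.

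**What to change.** In section 2.8.3, add region and teaching status to the primary model beside the baseline rate, and to every secondary-outcome model, including the one for safety improvement actions. Enter region as fixed effects, with regions that have very few centres pooled by a rule set before unblinding.

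The cost is one sentence. Region is known for every centre, and teaching status is already in Table 1. With seven regions and additive terms, the model spends 6 + 1 = 7 degrees of freedom (13 if the factors are fully crossed) out of about 115. If the strata explain nothing, the price is under 1 point of power: 96.4% against 96.0% in the simulation, which used the fully crossed indicators.
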